### Management protocol

No common management protocol will be imposed on the participating centers. However, most institutions have established a local protocol that is closely related to the most recent guidelines for the management of SE published by the American Epilepsy Society (AES) in 2016 [64].

In general, diagnosis of SE and related conditions is made based on clinical suspicion using physical examination and, where necessary, EEG (including, cEEG).

In most cases, emergency cerebral imaging with CT or MRI as well as standard emergency blood analysis, and CSF analysis if indicated, will be performed. Most frequently, the first treatment step consists of the administration of a benzodiazepine. If unsuccessful, intravenous administration of ASMs such as levetiracetam, valproate, (fos-)phenytoin, or lacosamide follows. As a third step, another ASM is added or anesthetics such as propofol or midazolam. All treatment decisions will remain at the discretion of the attending physicians.

The use of data acquisition sheets for the very early stages SE (Annex; modified from [56]) and ASM trials for IIC, which are already in place in some centers, will be encouraged to facilitate homogenous and complete data collection.

All participating centers perform cEEG for the following indications:

Management of refractory and super-refractory SE.Suspicion of NCSE after a convulsive SE or seizure (lack of return to neurological baseline).

Some participating perform cEEG for additional indications, such as patients unexplained altered mental status, detection of delayed cerebral ischemia in aneurysmal, subarachnoid hemorrhage.

The availability of cEEG is specific to each center, varying from 7 days a week (including Sundays and holidays) to during working hours on weekdays.

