The overarching goal of the Sustained Effort Network for Treatment of Status Epilepticus/European Academy of Neurology Registry on Refractory Status Epilepticus (SENSE-II/AROUSE) is to harmonize the collection of clinical and EEG data from multiple centers on SE to gain further insight on the management of SE across all its semiologies and etiologies, and to compare second- and third-line treatments and beyond. More specifically, we aim to:

identify risk factors of outcome, refractoriness, super-refractoriness.perform comparative effectiveness studies on third-line treatment and beyond, and on the use of cEEG.collect epidemiological data on rare forms and causes of SE.identify key targets for future randomized controlled trials.

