### Clinical data

Variables in Tables 1, 2 and 3 will be collected.

**Table 1 Tab1:** Baseline, SE-related and outcome variables; SE: Status Epilepticus; mRS: modified Rankin Scale; ILAE: International League Against Epilepsy; NCSE: non convulsive status epilepticus; EMSE score: Epidemiology Based Mortality Score in Status Epilepticus

**Demographics and premorbid status**	Age at admission, gender, ethnicity Estimated weight on admission. Location at SE onset Date and time of hospital admission Premorbid Clinical Frailty Scale [60] and premorbid mRS [61]
**Health variables**	History of previous seizures/epilepsy, history of SE Relevant known health problems (comorbidities) as found in Charlson comorbidities index [62]
**SE-related variables** General	Date and time of SE onset Refractory and super-refractory SE Date and time of refractoriness and super refractoriness
Semiology	Semiology according the ILAE [1] Worst seizure type according to STESS score [63] Level of consciousness at SE diagnosis or onset
Etiology	Etiology according to the ILAE and according to the EMSE score SE episode fulfilling criteria of New Onset Refractory Status Epilepticus (NORSE) or Febrile Infection-Related Epilepsy Syndrome (FIRES) [7]
**EEG-related variables**	Date of ictal EEG (if applicable) EEG pattern *(according to the ACNS 2021 terminology and Salzburg criteria for NCSE)* [2, 58, 59] EEG findings as classified in EMSE score [50] If NCSE was diagnosed by EEG and clinical response to IV ASM, then the ASMs and the timing and kind of EEG and clinical improvement are documented. Use of cEEG or repeated EEG in management/diagnosis Used EEG-target for CIVAD : seizure suppression, burst-suppression or flat EEG
**Performed diagnosis procedures**	Brain CT or MRI, continuous video-EEG monitoring (cEEG), fluorine-18 fluorodeoxyglucose (FG) brain positron emission tomography (PET) scan, cerebrospinal fluid analysis, antineuronal antibodies research, brain biopsy, therapeutic drug monitoring, Multimodal Invasive Monitoring or other.
**Outcome-related variables**	Date and time of SE cessation and EEG-documentation of SE cessation Date and time of first-time following commands Date of discharge from hospital mRS at discharge and at 30 days after admission (if still hospitalized) At 90 days after discharge: mRS, recurrence of seizure, ongoing ASM therapy Date and cause of death Reason for withdrawal of life support therapies

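### Continuous EEG (cEEG) is a named comparative-effectiveness exposure, but the listed variables give it no start or stop time, so it cannot be analysed as time-dependent and an ever- versus never-cEEG contrast would be biased

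*Protocol article*

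**What the plan says.** The aims at the end of the Background include a plan to "perform comparative effectiveness studies on third-line treatment and beyond, and on the use of cEEG".

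The Management protocol section imposes no common protocol but describes shared practice: "All participating centers perform cEEG for the following indications". The first indication is "Management of refractory and super-refractory SE"; the second is suspected nonconvulsive SE after a convulsive SE or a seizure. Some centres also "perform cEEG for additional indications". On cover, it says: "The availability of cEEG is specific to each center, varying from 7 days a week (including Sundays and holidays) to during working hours on weekdays".

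The Clinical data section states that the variables of Tables 1 to 3 are the ones collected. cEEG appears in Table 1 in two places:

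- in the EEG row, as "Use of cEEG or repeated EEG in management/diagnosis";
- in the row of diagnostic procedures performed, as an item of its own.

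Neither entry has a start or stop date or time. The only dated item in the EEG row is the date of the ictal EEG, without clock time. By contrast, Table 1 records date and time for SE onset, refractoriness, super-refractoriness and SE cessation. Tables 2 and 3 do the same for the start of antiseizure drugs, anaesthetic infusions, inhalational drugs, immune and additional therapies, intubation and vasopressors.

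**The concern.** Where cEEG is indicated by refractoriness, patients who receive it differ from those who do not in the feature that most plausibly drives outcome. That is confounding by indication across the whole cohort.

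Restricting to refractory SE does not remove the problem. At a centre with weekday-hours cover, a patient who becomes refractory on a Friday night must still be in SE on Monday to be exposed. If SE ends, or the patient dies, before then, the patient counts as never-cEEG. Exposure status then depends partly on how long SE lasted, and the waiting time of exposed patients is immortal with respect to SE cessation.

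The standard remedy is to treat cEEG as a time-dependent exposure, which needs a start time. An analysis plan written later cannot recover a start time that was not collected. Collection is prospective, so each case entered without it needs chart retrieval or loses the information.

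**Working it through.** **Plan's own figures.** The Sample size section takes a 50% refractoriness rate: 3000 × 0.50 = 1500 refractory patients, which reproduces. It states no figure for the cEEG comparison, so everything below is illustration under assumptions, always with no true cEEG effect.

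**Step 1: whole cohort, confounding by indication.** Let a be the share of refractory patients who get cEEG and b the share of other patients. With 50% refractory:

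- refractory share among cEEG patients = 0.5a / (0.5a + 0.5b) = a / (a + b)
- refractory share among the rest = (1 − a) / [(1 − a) + (1 − b)]
- spurious difference = (first − second) × outcome gap between refractory and other SE

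Assumed: a gap of 10 points (the 10% effect size in the Sample size section, borrowed as an assumption), and the values of a and b.

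| a | b | cEEG group | no-cEEG group | spurious difference |
|---|---|---|---|---|
| 1.00 | 0.10 | 0.909 | 0 | 9.1 points |
| 0.85 | 0.30 | 0.739 | 0.176 | 5.6 points |
| 0.70 | 0.10 | 0.875 | 0.250 | 6.2 points |
| 0.70 | 0.30 | 0.700 | 0.300 | 4.0 points |

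These are crude figures. Adjusting for refractoriness, which is recorded, would address this part.

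**Step 2: within refractory SE, extreme case.** Assumed: all patients at a weekday 08–17 h centre; refractoriness uniform over the week; cEEG started 1 h after the next open slot if SE is still ongoing; exponential remaining SE duration; no deaths. Simulation of 400,000 episodes, SE ended within 24 h:

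| median duration | ever cEEG | never cEEG | gap |
|---|---|---|---|
| 12 h | 63% | 92% | 29 points |
| 24 h | 37% | 83% | 46 points |

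Grouping the same simulated patients by whether cEEG was available when they became refractory gives 75% v 75% and 50% v 50%.

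**Step 3: within refractory SE, milder case.** Assumed: lognormal duration (median 12, 24 or 48 h; log-SD 1.0 or 1.5); half of patients at always-available centres and half at weekday 08–18 h centres; probability of poor outcome depends on SE duration only. 400,000 patients per scenario:

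| median, log-SD | never-cEEG share | poor outcome, ever v never | gap | by availability (unavailable v available) |
|---|---|---|---|---|
| 12 h, 1.0 | 17.8% | 37.4% v 32.0% | 5.4 | 36.3% v 36.5% |
| 12 h, 1.5 | 17.5% | 38.7% v 29.0% | 9.7 | 37.0% v 37.0% |
| 24 h, 1.0 | 11.5% | 43.7% v 35.9% | 7.8 | 43.0% v 42.6% |
| 24 h, 1.5 | 12.7% | 44.8% v 31.7% | 13.1 | 43.1% v 43.2% |
| 48 h, 1.0 | 6.3% | 50.1% v 39.4% | 10.7 | 49.4% v 49.4% |
| 48 h, 1.5 | 8.1% | 50.8% v 34.1% | 16.7 | 49.5% v 49.4% |

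The ever/never gap is 5 to 17 points. By availability it is at most 0.4 points.

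**Step 4: deaths.** Steps 2 and 3 contain none. Adding death during SE to the exponential model, at an assumed hazard one-tenth of the cessation hazard, gives death within 48 h of 8.4% v 9.1% (median 12 h) and 6.3% v 9.1% (median 24 h), ever v never cEEG. That gap favours cEEG, the opposite direction to Step 3.

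**The case against.** A reader might infer that the cEEG aim has no valid comparator at all. The document does not support that. Availability varies between centres and over the week, and refractoriness is timed, so refractory patients can be grouped by availability at that moment. Steps 2 and 3 show that this contrast is close to unbiased under their assumptions.

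A reader might also infer that the no-cEEG group is made up only of patients who were not refractory or whose SE ended early. That is not shown either. An indication is not proof of receipt, no common protocol is imposed, and patients with suspected nonconvulsive SE who are not refractory can get cEEG. The group is likely enriched for early resolution, not defined by it. Nor is cEEG recorded only in pooled form: the procedures row lists it alone, so any versus no cEEG is identifiable.

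The article fixes no ever/never analysis. The Objectives questions do not name cEEG effectiveness, and the Discussion names a comparative-effectiveness study only for third-line treatment and beyond. Comparator and time zero may sit in a fuller protocol or analysis plan, and their absence here is no fault. The data form is not shown, and other procedures in the same row are also untimed.

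The larger gaps are a worst case. With half of patients at always-available centres and 10–30% of patients missing cEEG for other reasons (assumed), the Step 2 gaps fall to about 12–17 points (median 12 h) and 16–27 points (24 h).

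All of this stands, and it narrows the point. It does not remove it: the tables are specific about timing for nearly every treatment, and an exposure named in the aims has none. An untimed exposure limits any later analysis plan, whatever contrast is chosen.

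**Conclusion.** The point holds in a limited form. From the listed variables, cEEG cannot be analysed as a time-dependent exposure. The patient-level contrast those variables most directly support, ever versus never cEEG, would be open to confounding by indication and, within refractory SE, to immortal-time bias.

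With no true effect, cEEG would appear associated with longer SE. That cEEG would appear to worsen outcome generally does not follow: early deaths also stay unexposed, so the direction for mortality is uncertain.

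The size cannot be read from the document. It is 5 to 17 points in poor outcome if outcome depends only on SE duration and half of patients are at weekday-hours centres. It reaches 29 to 46 points in SE ended by 24 h only if every centre has weekday-hours cover, uptake is complete and nobody dies. Durations, uptake and centre mix are all assumed. This is an inexpensive improvement to a stated aim, not a defect that invalidates the registry.

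**What to change.** - In Table 1 and the data form, record cEEG and repeated routine EEG as separate items, with start and stop date and time for cEEG.
- For the cEEG comparison, restrict to refractory SE, set time zero at the recorded date and time of refractoriness, and treat cEEG as time-dependent from its start.
- As a sensitivity analysis, compare refractory patients by whether cEEG was available at their centre at time zero, regardless of receipt. This needs each centre's hours of cover to be documented, and allowance for centre and out-of-hours differences in care.
- State that no cEEG effect will be based on ever- versus never-cEEG contrasts across the whole cohort.

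The cost is a few REDCap fields, one paragraph of analysis text and some extra data entry. The cEEG analysis set shrinks from about 3000 to about 1500 planned patients. Care is unaffected, since only timing of what is already done is recorded.

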### Data security and quality assessment

Recorded data are pseudonymized using site-specific sequential alphanumeric codes known to the local investigators only. Data entry is compliant with General Data Protection Regulation (GDPR) 2016/679 of European Union law. In countries where more restrict data protection rules are in place, only anonymized data will be provided.

Data collection will be performed using Research Electronic Data Capture (REDCap) electronic data capture tools hosted at Erasme Hospital [65, 66] REDCap is a secure, web-based software platform designed to support data capture for research studies, providing (1) an intuitive interface for validated data capture, (2) audit trails for tracking data manipulation and export procedures, (3) automated export procedures for seamless data downloads to common statistical packages, and (4) procedures for data integration and interoperability with external sources. Data are collected prospectively from the admission of the patient to discharge. Documentation must be started latest at the third working day after treatment to guarantee data quality. In some centers, data collection will be not feasible for a limited number of weeks for organizational reasons. These times will be communicated in advance to the steering committee. However, in the other time the consecutive inclusion of patients will be guaranteed.

Center participation will be monitored by a study coordinator to ensure consecutive case assessment and timely data entry. An independent data monitoring committee will periodically review data entry for completeness and accuracy. Any query due to missing data or lack of consistency will be resolved with local investigators.

### Ethics approval

The local ethics committee of each participating center approved the final study protocol. The following ethics committees reviewed and approved the study.

The study was registered at the Ethics Committee of Erasme Hospital (Committee Reference Number: 406; Protocol Number: CCB: B4062020000170; P2020/483).

The study was also registered in PRS with number NCT05839418.

In Switzerland, the collected data being part of this registry will not be used for research purpose (analyzed or published) without the formal approval by the Regional Research Ethic Committee (Ethikkommission Nordwest- und Zentralschweiz for Basel -EKNZ- and Commission Cantonale d’Ethique de la Recherche sur l’être humain for Geneva -CCER-).

This study will be performed in line with the principles of the Declaration of Helsinki.

### Informed consent

In some countries, informed consent was waived due to the non-interventional character of this study. In other countries, informed consent is obtained as early as possible once the patient recovers from SE. If a patient does not recover and a legal representative is available, then this legal representative will provide informed consent. This rule also applies if a legal representative or a health care proxy has already been in place before SE occurred. If the patient dies, data are included for ethical reasons in terms of safety considerations. Informed consent is particularly necessary for the telephone call 90 days after discharge in some countries. If no informed consent can be obtained, the patient will only be logged as event but medical data will be deleted in some countries.

In some countries, informed consent is necessary purely due to the prospective nature of this study and due to data sharing regulations, strictly adhering to the local regulations regarding secondary usage of data collected for the routine clinical care.

### Sample size

In the first prospective registry SENSE [51, 52], refractoriness rate reached 50%. Recent retrospective studies, single-center or population-based, showed a super-refractoriness rate from 3 to 10% [49, 67] using criteria defined above.

Thus, a cohort of approximately 3000 patients will be needed to reach a group size of 1500 patients in the refractory group and of about 150 patients in the super-refractory group.

For the refractory group, this group size is necessary to assess over 50 possible factors associated with outcome with a two-sided significance level of 5%, a power of 80% and an anticipated effect size of 10%.

For the super-refractory group, this group size will be needed to assess approximately 15 possible predictors of outcome with a two-sided significance level of 5%, a power of 80% and an anticipated effect size of 10%.

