**Methods:**

Sustained effort network for treatment of status epilepticus/European Academy of Neurology Registry on refractory Status Epilepticus (SENSE-II/AROUSE) is a prospective, multicenter registry for patients treated for SE. The primary objectives are to document patient and SE characteristics, treatment modalities, EEG, neuroimaging data, and outcome of consecutive adults admitted for SE treatment in each of the participating centers and to identify factors associated with outcome and refractoriness. To reach sufficient statistical power for multivariate analysis, a cohort size of 3000 patients is targeted.

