## Discussion

SENSE allowed to include over 1000 patients with SE from 8 centers. The study provided real-life data about SE and in particular refractory SE [54, 55].

It confirmed that a large proportion of first-line treatments was underdosed compared to the guidelines [54]. First-line treatment did not include benzodiazepines in 20% of all cases, 6% and 22% in CSE and non-CSE, respectively. These findings strongly suggest that IV ASMs are less efficacious than benzodiazepines as first-line treatment. Several predictors of SE cessation have been identified, such as a younger age, a lower mRS before SE onset, lower number of comorbidities, benzodiazepine as first-line treatment and a higher cumulative dose of ASMs within the first 30 min [53, 54]. Refractoriness occurred in 55% of patients and was associated with a higher baseline mRS and treatment deviation from guidelines, such as a lower bolus dose than recommended [54]. Unlike other studies, no difference was found comparing etiologies of refractory and non-refractory SE. Variables associated with good outcome in RSE were lower SE Severity Score (STESS) at SE onset, a shorter SE duration, a shorter length of stay and a lack of intubation. More than 70% of refractory SE were treated without airways protection and or mechanical ventilation. Limitations mentioned by the authors were the variability in recruitment of patients through the different centers, who could decrease the cohort homogeneity and potentially impacting on generalizability. Continuous EEGs were not available for most patients, even though it was recommended by several scientific societies [64, 68]. The focus of SENSE was RSE but only a few SRSE were recruited.

SENSE-II/AROUSE will provide high-quality data on SE of all types and severities. We have planned to collect continuous EEG data, if applicable, to alleviate the lack of knowledge about electrographic patterns of NCSE. We will focus on the functional outcome of SE but also on the refractoriness and super-refractoriness to identify potential predictors. Finally, due to lack of studies of third-line treatment and beyond, we plan to perform a comparative effectiveness study based on the collected data.

The evaluation of a large, heterogeneous patient group will hopefully help in clinical decision making in an area where data with higher level of evidence are still lacking.

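### The sample-size section gives the same 5% level, 80% power and 10% effect for 1500 refractory and about 150 super-refractory patients; no single definition of the 10% makes both the required size

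*Protocol article*

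**What the plan says.** The Methods paragraph of the abstract rests the cohort size on power: "To reach sufficient statistical power for multivariate analysis, a cohort size of 3000 patients is targeted". The Sample size section derives two subgroups from those 3000 patients: "a group size of 1500 patients in the refractory group", from a refractoriness rate of 50%, and a second "of about 150 patients in the super-refractory group", after citing earlier studies that "showed a super-refractoriness rate from 3 to 10"%.

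It then makes two power statements. For refractory patients, "this group size is necessary to assess over 50 possible factors associated with outcome with a two-sided significance level of 5"%, with 80% power and a 10% effect. For super-refractory patients, the group size is said to be needed for "approximately 15 possible predictors of outcome with a two-sided significance level of 5%, a power of 80% and an anticipated effect size of 10"%.

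Only the group size and the number of factors differ between the two statements. Neither says what the 10% measures, and no outcome rate, factor prevalence, test or formula is given. The Data analysis section plans chi-squared or Fisher tests between outcome categories for categorical variables, followed by multivariable models of unstated type.

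**The concern.** Power to detect a given effect of one factor is governed by the number of patients (or events), the outcome rate and the factor's prevalence. The number of other factors studied matters only through lost degrees of freedom or an adjusted significance level. One set of level, power and effect should therefore lead to broadly the same required size in both groups, yet the section gives sizes that differ tenfold.

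The super-refractory group is where the registry hopes to add most. The Discussion says of the earlier registry: "The focus of SENSE was RSE but only a few SRSE were recruited". If 150 patients have well under 80% power for the effect intended, real predictors will often be missed, and a null result could be read as coming from an adequately powered analysis.

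**Working it through.** **Inputs from the Sample size section.** Two-sided 5%, power 80%, effect 10% (scale undefined), N = 1500 with over 50 factors, N = about 150 with about 15 predictors, super-refractory rate 3% to 10%.

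**Assumptions, because the article gives no values.** A binary outcome with rates near 50% and a factor present in half the patients. Ranges follow.

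**Step 1: try to reproduce the stated 80%, reading 10% as an absolute difference.** This reading is closest to the planned chi-squared comparisons.

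Power = Φ[(|p2 − p1| − 1.96·s0)/s1], where s0 = √[p̄(1 − p̄)(1/n1 + 1/n2)] and s1 = √[p1(1 − p1)/n1 + p2(1 − p2)/n2].

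- N = 150, 45% vs 55%: s0 = 0.0816, s1 = 0.0812, (0.10 − 0.160)/0.0812 = −0.74, power 23%.
- N = 1500, same rates: s0 = 0.0258, s1 = 0.0257, (0.10 − 0.0506)/0.0257 = 1.92, power 97%.
- N for 80% power: per half, [(1.96·√0.5 + 0.842·√0.495)/0.10]² = 391.3, so about 783 in total.

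Neither 150 nor 1500 is reproduced.

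**Step 2: vary the assumed rates and split at N = 150.**

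| Rates | Factor in half | Factor in 20% |
|---|---|---|
| 45% vs 55% | 23% | 16% |
| 20% vs 30% | 29% | 17% |
| 10% vs 20% | 40% | 21% |
| 5% vs 15% | 53% | 25% |

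Even in the extreme case of 0% vs 10% with an even split, power only just reaches 81%.

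**Step 3: other meanings of 10%.**

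| Meaning | Power at 150 | Power at 1500 | N for 80% |
|---|---|---|---|
| Correlation r, or w, of 0.1 | 23% | 97% | 783–785 |
| Standardised mean difference 0.1 | 9% | 49% | 3140 |
| Relative 10% (50% vs 55%) | 9% | 49% | not computed; more than 1500 |
| Partial f² or R² of 0.10, one predictor | 97–98% (15 in model) | over 99% (50 in model) | 74–84 |
| f² or R² of 0.10, overall test | 63–69% (15 predictors) | over 99% (50 predictors) | 183–201 (15), 308–338 (50) |

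The regression rows use the noncentral F distribution with noncentrality f²·N. No row makes both 150 and 1500 the required size.

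**Step 4: can the number of factors explain the gap?** Take a Bonferroni adjustment as the most favourable case. The critical values are 2.935 for 15 tests and 3.291 for 50. At any fixed effect the required sizes stand in the ratio [(3.291 + 0.842)/(2.935 + 0.842)]² = (4.133/3.777)² = 1.20, not 10. For a 10-point difference (20% vs 30% up to 45% vs 55%), 50 tests need about 1280 to 1700 patients, which is near 1500. The same rule for 15 tests needs about 1070 to 1420, not 150. In the overall regression test the step from 15 to 50 predictors raises N by about 1.7 times (183 to 308).

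**Step 5: detectable difference at 80% power** (absolute difference centred on 50%, factor in half). Approximately 2.80/√N; the exact solutions are:

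| N | Source | Detectable difference |
|---|---|---|
| 1500 | stated refractory group | 7.3 points |
| 300 | 10% of 3000 | 16.2 points |
| 150 | stated super-refractory group | 22.7 points |
| 90 | 3% of 3000 | 29.2 points |

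**The case against.** A reader might infer that the super-refractory claim is simply false because 150 patients give 23% power. The article does not support that. The 23% needs an absolute 10-point difference, rates near 50% and an even split, none of which it states. If the 10% is a partial f² or R² for one predictor, 150 patients with 15 predictors give about 97–98% power. With a Bonferroni adjustment over 15 this becomes about 81–86% (76% for f² under another noncentrality convention), so 80% could be met in both groups. This part of the objection stands. It does not rescue the section: on that reading about 80 patients suffice without adjustment, and 1500 are far from necessary.

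The two calculations might also have used very different undisclosed inputs. On the 10-point reading with rates near 50%, 1500 fits a factor present in about 15% of patients (783 × 0.25/(0.15 × 0.85) = 1535). But 150 needs something close to 0% vs 10% in an even split. Nothing in the section suggests such a difference.

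The ratios 1500/50 = 30 and 150/15 = 10 may tempt a reader to see a patients-per-variable rule behind the numbers. That is conjecture, and the two ratios do not match one rule. Nor is 150 itself an error: it is 5% of 3000, inside the cited range. Multiplicity control, event counts per predictor and choice of regression method may be settled in a document not shown, and form no part of this point.

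Finally, this is an observational registry with descriptive aims, and an article may leave inputs to a fuller document. But the article does more than omit inputs: it prints two power statements that conflict.

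**Conclusion.** The point holds as an inconsistency and a failure of reproducibility. Identical level, power and effect are said to require sizes that differ tenfold; no single definition of the effect delivers both, and the number of factors accounts for a ratio of about 1.2 (Bonferroni) to 1.7 (overall test). As printed, at least one statement is wrong.

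Which one is wrong depends on the undefined 10%. On the reading closest to the planned tests, the super-refractory claim fails: about 23% power with rates near 50% and an even split, and about 16% to 53% over the other rates and splits tried. On the partial f² or R² reading, it is the necessity of 1500 that fails. The registry's value as a descriptive cohort is not in question.

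**What to change.** Restate the Sample size section with the effect measure, the assumed outcome rate and the assumed factor prevalence. Give the detectable difference at 80% power for each group. If an absolute difference is meant, with rates near 50% and a factor in half the patients, these are about 7 points for 1500 and about 23 points for 150, with 29 points for 90 and 16 for 300 to cover the cited 3% to 10% rate in 3000. If another measure is meant, give the equivalent figures on that scale.

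Unless 80% power in super-refractory patients can be reproduced on the stated measure, withdraw that claim and label the analysis as estimation or exploratory. Bring the abstract's sentence on power into line.

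The cost is a reworded paragraph and probably a less favourable stated figure. No extra patients or data are needed.
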